# The DEXACELL trial—a protocol for a pragmatic, multicentre, double-blind, placebo-controlled, randomised, parallel group, phase 3 superiority trial to assess the effectiveness and cost-effectiveness of DEXAmethasone as an adjunctive therapy for the management of CELLulitis in adults presenting to urgent secondary care in the UK

**DOI:** 10.1136/bmjopen-2025-109953

**Published:** 2025-10-29

**Keywords:** Randomized Controlled Trial, DERMATOLOGY, Emergency Departments, HEALTH ECONOMICS, PAIN MANAGEMENT, Drug Utilization

## Abstract

**Introduction:**

Cellulitis is a common bacterial skin infection causing significant pain, swelling and impact on daily activities, frequently leading to emergency department presentations and hospital admissions. While antibiotics are the mainstay of treatment, they do not directly address inflammation, often resulting in persisting or worsening symptoms in the initial days. Corticosteroids, with their potent anti-inflammatory effects, have shown benefit in other acute infections but are not currently standard care for patients with cellulitis. This trial aims to determine if adjunctive oral dexamethasone can reduce pain and improve outcomes in adults with cellulitis presenting to UK urgent secondary care settings.

**Methods and analysis:**

This is a pragmatic, multicentre, double-blind, placebo-controlled, randomised, parallel group, phase 3 superiority trial, with an internal pilot and parallel health economic evaluation. Adult patients (≥16 years) with a clinical diagnosis of cellulitis (at any body site except the orbit) presenting to urgent secondary care will be screened for eligibility. 450 participants will be randomised (1:1) to receive either two 8 mg doses of oral dexamethasone or matched placebo, administered approximately 24 hours apart, in addition to standard antibiotic therapy. The primary outcome is total pain experienced over the first 3 days postrandomisation, calculated using the standardised area under the curve from pain scores (Numerical Rating Scale 0–10) across up to seven timepoints. Secondary outcomes include health-related quality of life (EuroQol 5 Dimension 5 Level), patient global impression of improvement, analgesia and antibiotic usage, hospital (re)admissions, complications, unscheduled healthcare use, cellulitis recurrence and cost-effectiveness at 90 days. The primary estimand will apply a treatment policy approach to intercurrent events.

**Ethics and dissemination:**

The trial has received ethical approval from South Central—Oxford B Research Ethics Committee (reference: 24/SC/0289) and will be conducted in compliance with Good Clinical Practice and applicable regulations. Informed consent will be obtained from all participants. A model consent form can be seen in online supplemental file S1. Findings will be disseminated through peer-reviewed publications and conference presentations, and to patient groups and relevant clinical guideline committees.

**Trial registration number:**

ISRCTN76873478.

STRENGTHS AND LIMITATIONS OF THIS STUDYThis trial employs a robust double-blind, placebo-controlled design to minimise bias in assessing a subjective primary outcome (patient-reported pain).The pragmatic nature of the trial, recruiting from diverse urgent secondary care settings, with additional incentives to recruit from minoritised groups, aims to enhance the generalisability of findings to real-world clinical practice.Comprehensive follow-up to 90 days allows for assessment of both short-term symptom relief and longer term impacts on healthcare utilisation and recurrence.The inclusion of a parallel health economic evaluation will provide crucial information on the cost-effectiveness of adjunctive dexamethasone.Potential variability in ‘usual care’ antibiotic regimens across sites, while reflecting real-world practice, is a possible limitation, which is accounted for in the pragmatic design.

## Introduction

### Background and rationale

 Cellulitis, a common bacterial infection of the skin and subcutaneous tissues, imposes a substantial burden on both patients and healthcare systems.^1^ It is characterised by pain, swelling, erythema and warmth, often leading to reduced mobility and ability to perform daily activities. In England alone, cellulitis accounts for over 300 000 presentations to Emergency Departments (EDs) annually, with approximately 50% of these patients requiring hospital admission.^2^ Patients with cellulitis represent about 3% of all adult hospital admissions and are estimated to occupy 1% of National Health Service (NHS) hospital beds in England and Wales.^3^

Standard UK management of cellulitis involves antibiotic therapy, analgesia and elevation of the affected limb.^4^ Despite antibiotic treatment aimed at eradicating the bacterial cause, the associated inflammation can persist or even worsen in the initial 48–72 hours.^5^ This ongoing inflammation often manifests as significant pain, which is a major reason for patient reattendance at hospitals or other healthcare providers, occurring in approximately one in five patients.^6 7^ Such representations can lead to extended or alternative antibiotic courses, which may offer no additional benefit while contributing to increased costs and antibiotic resistance.^8 9^ There is therefore interest in improving early symptomatic response in cellulitis by modulating the host inflammatory response.

Oral corticosteroids are well-established anti-inflammatory agents shown to be effective in numerous other acute infectious and inflammatory conditions to dampen the immune response and improve short-term symptoms. For example, systematic reviews have shown benefits of adjunctive corticosteroids in conditions like sore throat and in croup.^10 11^ Two previous randomised trials have investigated corticosteroids for acute cellulitis. One Danish trial (n=112) found that prednisolone (30 mg daily, reducing over a week) significantly reduced time to clinical cure compared with placebo (10.0 vs 14.6 days, p<0.01), with no evidence of increased recurrence of cellulitis at 1 year follow-up.^12 13^ An unpublished trial (NCT01671423, n=25) reported a non-statistically significant trend towards greater pain reduction at 48 hours with a single dose of 60 mg prednisolone versus placebo (mean change from baseline 39.9 vs 30.5 points on a 0–100 Visual Analogue Scale). Additionally, trials of non-steroidal anti-inflammatory drugs (NSAIDs), which may have a similar mechanism of action to corticosteroids, have suggested a benefit in cellulitis.^14^ However, there are concerns about the adverse effects of NSAIDs, and so these were not considered in this trial. Current guidelines from the Infectious Diseases Society of America (IDSA) acknowledge the potential for corticosteroids for the treatment of cellulitis but call for further high-quality randomised controlled trials to establish the role of corticosteroids in cellulitis management, a position also echoed by Cochrane.^15 16^

The DEXACELL trial is designed to address this evidence gap. It is a pragmatic, multicentre, double-blind, placebo-controlled, randomised, parallel group, phase 3 superiority trial with an internal pilot phase and a parallel health economic evaluation.

The primary research question is: *Is the addition of oral dexamethasone to usual care in patients who present to urgent secondary care with cellulitis effective and cost-effective in terms of reducing pain, improving quality of life and reducing further antimicrobial usage and healthcare utilisation?* Given the high incidence of cellulitis, even a modest improvement in symptoms and/or a reduction in healthcare costs could have significant population-level benefits.

### Objectives

*Primary objective:* to establish if the addition of dexamethasone to treat patients presenting to urgent secondary care with cellulitis reduces total pain reported over the first 3 days (postrandomisation) compared with a control (placebo).

*Secondary objectives:* to determine whether the addition of dexamethasone, when compared with a control (placebo), to treat patients with cellulitis presenting to urgent secondary care with cellulitis: (a) improves quality of life and other patient-reported outcomes, (b) reduces subsequent antimicrobial prescribing, analgesia usage and healthcare utilisation and (c) is cost-effective.

## Methods and analysis

### Trial design and setting

This is a pragmatic, multicentre, double-blind, placebo-controlled, randomised, parallel group, phase 3 superiority trial with an internal pilot and parallel health economic evaluation. Potential participants will be identified and recruited from urgent secondary care services (e.g., ED, Ambulatory Care Units, Same Day Emergency Care) across up to 20 sites in the UK. After providing informed consent, participants will be individually randomised on a 1:1 ratio to receive either oral dexamethasone or matched placebo in addition to standard antibiotic therapy.

### Eligibility criteria

The eligibility criteria for the trial are detailed in table 1.

**Table 1 T1:** Inclusion and exclusion criteria

Inclusion criteria	Exclusion criteria
Participants must meet all of the following:	Participants must meet none of the following:
Aged 16 years old or over. A current clinical diagnosis of cellulitis at any body site except the orbit (periorbital/orbital cellulitis). Able to provide informed consent.	Orbital or periorbital cellulitis, surgical site infection or planned surgical management (eg, abscess) as managed under a different clinical pathway. Known allergy to dexamethasone. Contraindication to dexamethasone due to concurrent medication (e.g., cobicistat). Known current invasive fungal infection.* Known current gastric or duodenal ulceration. Already on systemic corticosteroids (other concomitant corticosteroids such as inhalers or creams are acceptable). Unable to take oral medication. Lack of capacity. Inability to complete follow-up procedures. Prisoner.†
People of childbearing potential must be willing to:	
Use a highly effective method of contraception (and must agree to continue 3 months after the last dose of the IMP).	
Inform the trial team if pregnancy occurs during trial participation.	
	People of childbearing potential only:
	Pregnant, breastfeeding or planning to conceive in the next 3 months.

* This includes only invasive infections such as pulmonary aspergillosis and does not include cutaneous infections such as athlete’s foot, vaginal thrush, etc.

† This does not exclude patients in police custody, though consideration should be given to whether they are able to complete the trial follow-up procedures.

IMP, Investigational Medicinal Product.

### Intervention and comparator

#### Intervention

Participants in the intervention group will receive two 8 mg doses of oral dexamethasone. The first dose will be administered as soon as possible after randomisation, while in the urgent secondary care unit. The second dose is to be taken 24 hours later (±6 hours). If discharged, participants will take the second dose at home; if hospitalised, it will be administered by clinical or research staff. Each 8 mg dose consists of two 4 mg dexamethasone tablets overencapsulated into two separate capsules for blinding purposes. No modification of trial dosage is permitted in the study.

Dexamethasone was chosen for its high glucocorticoid activity and recent clinical experience in trials like RECOVERY.^17^ The dose (8 mg), route (oral) and course (two doses) were based on expert opinion suggesting additional benefit of a second dose at ~24 hours for pain outcomes. Given its half-life, the selected regimen is expected to affect swelling and pain over the subsequent 24–48 hours.

#### Comparator

Participants in the comparator group will receive two doses of matched placebo capsules, identical in appearance and administered on the same schedule as the active drug. The placebo design is crucial to ensure blinding due to the participant-reported primary outcome.

#### Usual care

All participants will receive usual care for cellulitis as per local policy at each site, including clinical assessment, antibiotics and analgesia, hospital admission if required, advice on management of concomitant conditions and expected symptom duration. Details of any antibiotics and analgesia administered will be recorded at baseline and at day 14 follow-up.

#### Compliance

Intervention compliance for dose 1 and any reason for non-compliance will be recorded on the study database by site staff. Intervention compliance for dose 2 will be self-reported by participants via yes/no response to a short message service (SMS). Compliance rates will be monitored by the oversight committees.

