### Participant timeline

All screening, eligibility, consent and baseline data will be collected in-person during attendance to secondary urgent care. The participant will be asked to complete a short baseline questionnaire pack, and the study team will collect the remaining baseline data (see table 2). Once the minimum baseline data are collected (see data collection section), participants will be randomised and administered the first dose of their allocated intervention. Early follow-up (T1–T6) occurs via SMS survey approximately every 12 hours for the first 3 days, starting at the next available 8 am or 8 pm timepoint after randomisation. This includes the collection of pain scores to calculate the primary outcome plus some minimal data for secondary outcomes. Additional follow-up to collect secondary outcome data via telephone occurs at day 14 (±2 days) and day 90 (±7 days). Participants will be advised to use a paper diary/aide-memoire to record data to help them during the day 14 and day 90 follow-up calls.

**Table 2 T2:** Data collection and schedule of assessments

Assessment/event	Baseline (in person)	Early follow-up (text message survey*)						Late follow-up (telephone)	
	**Recruitment (time 0**)	**T1†**	**T2†**	**T3†**	**T4†**	**T5†**	**T6†**	**14 days** (**±2)‡**	**90** **days** (**±7)‡**
Enrolment**:**									
Eligibility screen	X								
Consent	X								
Demographics	X								
Anthropometry	X								
Contact details	X								
Contact preferences	X								
Comorbidities	X								
Cellulitis details	X								
Risk factors for steroid adverse events	X								
Frailty score (Rockwood),**^31^** if aged 65 or over	X								
Intervention/comparator:									
Randomisation	X								
Study drug dispensed§§	X								
Dexamethasone or placebo dose taken§§	X		X						
Intervention compliance data	X			X^+^					
Assessments:									
Current pain (NRS, 0–10)^+^	X	X	X	X	X	X	X	X	
PGI-I^+^			X		X		X	X	
EQ-5D-5L^+^	X						X	X	X
Analgesia usage	X							X	
Antibiotic usage	X							X	
Complications potentially related to dexamethasone								X	
(Re)admission to hospital								X	
Unscheduled healthcare usage^+^								X	
Health, social care, broader societal resource use^+^	X								X
Recurrence of cellulitis									X
Adverse event review								X	X

+Participant reported*.*

* SMS survey is the default option with options for face-to-face for inpatients or telephone call for outpatients if unable to complete SMS survey.

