† The first follow-up text message (T1) will be received at the first available follow-up timepoint (~8 am or ~8 pm) after randomisation, the subsequent five follow-up texts (T2–T6) will be received every 12 hours thereafter*.*

‡ The anchor point (day 0) is the date of randomisation.

§ The first dose of study drug will be given after baseline assessments and randomisation have been performed; the second dose will be taken ~24 hours later (±6 hours).

EQ-5D-5L, EuroQol 5 Dimension 5 Level; NRS, Numerical Rating Scale; PGI-I, Patient Global Impression of Improvement; SMS, short message service.

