Secondary continuous outcomes (PGI-I, pain at 14 days) will be analysed using mixed-effects linear regression models if assumptions are met; PGI-I at days 1, 2 and 3 will use a mixed-effects repeated measures model. Alternative modelling (eg, mixed-effects ordinal logistic models, dichotomisation for logistic regression) will be considered if assumptions are not met, detailed in SAP. Dichotomous secondary outcomes (additional antibiotic use, (re)admission, unscheduled healthcare use, recurrence) will be analysed using mixed-effects logistic models (if event numbers allow). All models will adjust for the same factors as the primary analysis. Adjusted differences in means or ORs (with 95% CIs) will be reported, along with unadjusted estimates.

Descriptive analysis will cover compliance, analgesia details, antibiotic details and dexamethasone-related complications. The estimands framework for secondary outcomes will mirror the primary outcome. Multiple imputation may be considered for missing secondary outcome data. SAEs will be reported descriptively by whether the first dose was taken (not intention to treat (ITT)).

Exploratory subgroup analyses on the primary outcome (not powered for) will be pre-specified for: cellulitis location (lower limb vs other) and NSAID usage at randomisation (user vs non-user). The primary analysis model will be refitted including an interaction term between treatment and the subgroup of interest; minimum numbers for these analyses will be pre-specified in the SAP.

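### The only dose-2 compliance question is sent at T3, often before the dose-2 window has closed, and no later item can correct an early no

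*Protocol article*

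**What the plan says.** - **Dosing (Intervention).** "The first dose will be administered as soon as possible after randomisation, while in the urgent secondary care unit". For dose 2: "The second dose is to be taken 24 hours later (±6 hours"). Participants who have gone home take it themselves; for those in hospital, staff give it.
- **How compliance is collected (Compliance).** Site staff record dose 1. For dose 2, "Intervention compliance for dose 2 will be self-reported by participants via yes/no response to a short message service (SMS").
- **When it is collected (Table 2, Participant timeline).** The row "Intervention compliance data" is marked at baseline and at T3, the T3 mark being flagged as participant reported. Nothing is marked at T4 to T6, day 14 or day 90.
- **When the texts arrive (Table 2 footnotes).** "The first follow-up text message (T1) will be received at the first available follow-up timepoint" (about 8 am or 8 pm) after randomisation, and "the subsequent five follow-up texts (T2–T6) will be received every 12 hours thereafter".
- **What compliance is used for.** "Compliance rates will be monitored by the oversight committees" (Compliance), and "Descriptive analysis will cover compliance, analgesia details, antibiotic details and dexamethasone-related complications" (Statistical methods).

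**The concern.** The single yes/no question can reach a participant while dose 2 is still validly outstanding. An honest no at that moment means not yet, but it is stored in the same form as a no from someone who never takes the dose. Whether this happens depends on the clock time of randomisation and on the delay to dose 1, not on adherence.

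What is at stake is how the compliance rate is read. The Discussion singles out adherence to the second, often home-taken dose as important, and the oversight committees watch this rate. If it is understated by an unknown amount, adherence could look worse than it is. An analysis plan cannot repair this later, because nobody is scheduled to be asked again.

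**Working it through.** The article gives no figure for this check, so there is none to reproduce. The timings follow from the article; the recruitment, delay, dosing and reply patterns below are assumptions.

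**1. Time of T3.** T1 is the next 8 am or 8 pm, so 0 to 12 h after randomisation. T3 = T1 + 24 h, so 24 to 36 h after randomisation.

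**2. Close of the dose-2 window.** Let dose 1 be given L hours after randomisation. The window runs from 24 − 6 = 18 h to 24 + 6 = 30 h after dose 1, so it closes 30 + L h after randomisation. The article gives no value for L. Some delay is allowed, because Data collection methods lets part of the baseline data be gathered between randomisation and dose 1.

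**3. Share asked before the window closes.** If randomisation times are even over the 12-hour cycle, T3 is uniform on 24 to 36 h, and

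P(T3 < 30 + L) = (6 + L)/12.

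This is 6/12 = 50% at L = 0 and 7/12 = 58% at L = 1 h. With L = 0 the participants concerned are those randomised between 2 pm and 8 pm or between 2 am and 8 am. For randomisation even over 9 am to 5 pm, T3 is uniform on 27 to 35 h and the share is 3/8 = 38%. For noon to 8 pm, T3 is uniform on 24 to 32 h and the share is 6/8 = 75%.

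T3 comes before the nominal 24-hour point only if dose 1 was delayed: the share is L/12 under even recruitment, which is 0% at L = 0 and 8% at L = 1 h.

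**4. Share that could be misrecorded.** This is smaller. The participant must reply before taking dose 2 and then take it inside the window. With L = 0, even recruitment, an immediate reply and dose-2 time uniform over the window:

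P = ∫ from 24 to 30 of (1/12) × (30 − t)/12 dt = 18/144 = 12.5%.

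If dose-2 times instead cluster around 24 h with an SD of 2 h, P ≈ 2 × 0.399/12 = 6.7%. If the uniform case is kept but the reply comes 1 h after the text, P = (5²/2)/144 = 8.7%.

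A simulation over the wider set of assumptions gave:

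| Randomisation times (even over) | Window still open at T3: L = 0 / L = 0–2 h | Reply precedes an in-window dose 2: L = 0 | Same, L = 0–2 h |
|---|---|---|---|
| 24 h, or 8 am–8 pm | 50% / 58% | 3.3–12.5% | 6.9–17.1% |
| 8 am–6 pm | 40% / 50% | 0.6–6.7% | 1.8–10.6% |
| 9 am–5 pm | 38% / 50% | 0.2–4.7% | 0.9–8.5% |
| noon–8 pm | 75% / 88% | 4.9–18.7% | 10.3–25.7% |

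L = 0–2 h means a delay uniform over that range. In each range the low end has dose-2 times with an SD of 2 h (held within the window) and a reply 1 h after the text. The high end has dose-2 times uniform over the window and an immediate reply. Every simulated participant replies, self-reports and takes dose 2 within the window.

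**5. Would T4 be late enough?** T4 = T1 + 36 h, so 36 to 48 h after randomisation. It follows the close of the window for everyone if 36 ≥ 30 + L, that is, for L up to 6 h.

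**The case against.** The strongest reply is that the article does not say what happens to a no. It gives no text wording, reply cut-off or classification rule, and such detail may sit in the full protocol or the data management plan. This stands. A reader might infer that late takers are recorded as non-compliant; the article supports only that they can be. Someone who answers the text after taking the dose would say yes. The schedule itself is not an omission, however: Table 2 states when the item is collected, and it is collected once.

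A reader might also take the 38% to 50%, or the higher figures with delayed dosing, as the share misrecorded. It is the share asked while the window is open. T3 is never earlier than 24 h after randomisation, so many of those asked will already have taken the dose.

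Other mitigations are fair. Staff give dose 2 to inpatients, so the problem falls mainly on discharged participants. Response times are recorded for the pain scores on the same texts, so an early no may be identifiable; but a time stamp does not show whether the dose was taken afterwards. The timing is the same in both blinded groups, so no difference between them is expected from this source.

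Two further inferences are not supported. One is that the error would feed an analysis by second dose received: none is described. Compliance is descriptive, and serious adverse events are reported by whether the first dose was taken. The other is that Table 2 contradicts the dosing window because it marks the second dose under T2 (12 to 24 h). The grid has only 12-hourly columns, T2 overlaps the window, and the footnote repeats the interval given under Intervention. That mark is schematic.

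**Conclusion.** The point holds, as a cheap improvement of modest importance. The timings in the article establish that the sole dose-2 question often arrives before the window has closed and that no later item is scheduled to correct an early no.

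The size rests on assumptions. With dose 1 given at randomisation, about 38% to 50% are asked with the window still open under daytime or even recruitment (75% if recruitment is concentrated between noon and 8 pm), and delay to dose 1 raises these shares. Potential misrecording is roughly 3% to 17% under even recruitment and 0.2% to 26% over everything tried. These percentages apply to participants who report dose 2 themselves, so the share of the whole trial is lower to the extent that staff give the dose.

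The consequence is limited to a compliance rate that is described and monitored. The primary estimand follows a treatment-policy approach, so recorded compliance does not enter the primary analysis.

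**What to change.** Keep the dose-2 question at T3. Repeat it at T4 for participants who answered no or did not reply at T3, and mark T4 in the compliance row of Table 2.

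T4 is already sent to everyone, so no extra contact is needed. The cost is a change to the text-message set-up, one table cell, one additional item for a minority on a text that already carries pain and PGI-I, and recall that is about 12 hours longer for those asked again. Keeping T3 preserves the shorter recall for everyone who has already taken the dose. No change to the dosing window is proposed.
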